### Interim analyses {21b}

There will be no interim analyses regarding the main objective of the trial. However, secondary or complementary analyses (e.g., correlational) of the baseline data can be performed.

### Methods for additional analyses (e.g., subgroup analyses) {20b}

The inclusion of CORE-OM will permit to assess the degree of therapeutic change with regard to psychological distress, psychosocial functioning, and suicide risk. Also, the application of CORE-SFB and SRS 3.0 in each session will allow to assess the change experienced in psychological distress and therapeutic alliance as a function of the number of sessions and the percentage of change session by session. We will conduct growth mixture modeling based on these weekly assessments to identify distinctive patterns of change and evolution of the therapeutic alliance. If several patterns can be identified, we will perform mixed linear models and repeated-measure analyses of variance to compare patients’ characteristics in each pattern, and we will identify possible associations between change in psychological distress and therapeutic alliance scores. Then, we will consider using multinomial logistic regression to compute predictive models for the patterns from patients’ characteristics. Also, we could use hierarchical linear regression to establish the power of each pattern to predict treatment outcomes. Subgroup analyses by gender will be explored to check if there are significant differences in the therapy course. Secondary analyses will explore the potential mediator or moderator role of the cognitive measures obtained by the RGT, especially those measures related with cognitive conflicts. Finally, if the results of the trial support our main hypotheses, a complementary protocol for qualitative analyses of therapy sessions’ verbatim will be issued in due time with the goal of exploring the change mechanisms.

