Several clinical guidelines point out that psychotherapy is the first-line treatment to address mild-to-moderate depression in teenagers and adults, and pharmacological treatments are reserved to more severe and complex cases that do not respond to psychotherapy [6]. Research about different treatments for depression highlights that psychological therapies are effective and contribute to preventing more severe and recurrent depressive disorders [7]. Regarding the theoretical orientation of the psychological treatments applied, the literature shows that cognitive behavioral therapy (CBT) is the approach that has published more studies, obtaining thus more prestige [8], whereas others claim that its efficacy is diminishing [9]. Indeed, current evidence is not conclusive about signaling one particular form of psychotherapy as clearly more effective than the others, and some reviews consider also other well-established psychological treatments [10], there is a lot of room for improvements (i.e., more than 40% do not respond, only 30% achieve a complete recovery, and relapse rates are high).

On the other hand, some research has pointed out some other factors than therapeutic orientation. Khan et al. [11] claimed that getting the patients engaged in an active therapeutic program was crucial, especially if we consider a dropout rate of 35% [12]. As the engagement in therapy relies on the preferences and attitudes of each patient, therapists might benefit from the availability of a variety of evidence-based psychotherapeutic alternatives. Along these lines, Cuijpers et al. [13] emphasized the importance of personalizing therapies. Another factor that supports the need for adapting the treatment to the patient’s preferences and characteristics is the therapeutic alliance (including the agreement on the therapy tasks), acting as the best predictor of success in virtually any therapy modality [14].

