### Interventions

#### Intervention description {11a}

Specific therapy protocols for the three treatment conditions of the study (CBT, PCT, and PCT-VR) have been developed. These three treatments will follow the same format: a maximum of 10 individual 1-h sessions, with one or two booster sessions at about 3 months after the tenth session. The protocols are not standardized since they are based on personalized case conceptualization. In both PCT and PCT-VR, the construction of self and others will be explored with the RGT; but while in the former, only 2D diagrams will be used (paper); in the latter, this will be done with EYME, in an immersive VR environment for each patient. A video with a brief illustration of the use of EYME in the treatment can be found at https://www.youtube.com/watch?v=aGOOo8p7EfM. Also, a brief description of the RGT procedure which will be applied in these two treatment conditions follows.

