### Methods in analysis to handle protocol non-adherence and any statistical methods to handle missing data {20c}

The analysis will follow an intention-to-treat strategy. As missing values will be lessened by Qualtrics quality control strategies, no imputation plan is considered in advance.

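### Repeated-measures ANOVA is a poor fit for comparing growth-mixture patterns: it needs a known group label and a complete series, and neither is assured; the mixed models already named should replace it

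*Protocol article*

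**What the plan says.** The section on additional analyses {20b} sets out a sequence based on the short CORE form and the Session Rating Scale, both completed at every session.

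- First: "We will conduct growth mixture modeling based on these weekly assessments to identify distinctive patterns of change and evolution of the therapeutic alliance".
- Then, on condition that several patterns are found: "we will perform mixed linear models and repeated-measure analyses of variance to compare" the characteristics of patients in each pattern.
- Next, tentatively: "we will consider using multinomial logistic regression to compute predictive models for the patterns".
- Last, also tentatively: "we could use hierarchical linear regression to establish the power of each pattern to predict treatment outcomes".

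Two other statements bear on this. The intervention description {11a} allows "a maximum of 10 individual 1-h sessions", so treatment courses may differ in length. The section on non-adherence and missing data {20c} says that "no imputation plan is considered in advance".

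The article does not say how patients are assigned to patterns, or which scores the repeated-measures ANOVA will be run on.

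**The concern.** A growth mixture model does not tell us which pattern a patient belongs to. It gives each patient a probability of belonging to each pattern. Classical repeated-measures ANOVA has no place for such a probability: it compares groups whose membership is taken as observed. It also needs a full row of repeated values per patient and discards anyone whose row is incomplete. A patient who finishes in fewer than ten sessions has an incomplete ten-session row even if every form was returned.

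The mixed linear models named in the same sentence keep patients with partial series. The ANOVA therefore adds nothing that they do not provide. If it is run on repeated scores, its results describe a selected group of patients. If an estimated pattern is then used as though it were known, there or in the later regressions, the associations may be biased and the standard errors leave out the uncertainty in classification.

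**Working it through.** The article gives no figure for these analyses, so there is nothing to reproduce. The checks below use N = 225 from the sample size section {14}, the cap of ten sessions, and assumed ranges for what is not stated.

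**1. Patients with a complete row.** Let m be the chance that one form is missing, independently across forms, for a patient with ten sessions. The complete share over ten sessions is (1 − m)^10.

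| m (assumed) | (1 − m)^10 | Complete, of 225 |
|---|---|---|
| 1% | 0.904 | 203 |
| 2% | 0.817 | 184 |
| 5% | 0.599 | 135 |
| 10% | 0.349 | 78 |

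At m = 5% the loss is 1 − 0.599 = 0.40. If the planned 5% dropout also leaves incomplete series, the complete share is 0.95 × 0.599 = 0.57, or 128 patients.

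If the ANOVA is instead meant for measures taken at baseline, post-treatment and six months (Table 1), with baseline complete, the share is (1 − m)^2. That is 0.95² = 0.90 (203 patients) at 5% and 0.90² = 0.81 (182 patients) at 10%. The loss is much smaller on that reading, but the mixed model is still the better method.

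**2. Pattern treated as known, compared variable unrelated to the trajectory within class.** Let a be the share of patients classified correctly.

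- Two equal classes: each assigned group contains a share a of its own class and 1 − a of the other, so the observed difference is the true one times a − (1 − a) = 2a − 1.
- Three equal classes with symmetric error: the factor is a − (1 − a)/2.

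| a (assumed) | Two classes | Three classes |
|---|---|---|
| 0.95 | 0.90 | 0.93 |
| 0.90 | 0.80 | 0.85 |
| 0.85 | 0.70 | 0.78 |
| 0.80 | 0.60 | 0.70 |
| 0.70 | 0.40 | 0.55 |

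In this case the bias is towards zero. A simulation (N = 225, 2,000 replicates, class boundary known) agrees: accuracy 0.84 gave 0.68 and accuracy 0.93 gave 0.85.

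**3. Compared variable correlated with the trajectory within class.** This is plausible when session distress defines the pattern and later BDI-II is the outcome. Take two equal classes 2 SD apart, cut at the midpoint, a true outcome difference of 0.5 SD, and within-class correlation ρ.

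- Accuracy is Φ(1) = 0.841, so 2a − 1 = 0.683.
- The cut also selects on the within-class deviation. Its mean differs between the assigned groups by 4φ(1) = 4 × 0.242 = 0.968.
- The factor is 0.683 + ρ × 0.968/0.5 = 0.683 + 1.936ρ.
- ρ = 0 gives 0.68, ρ = 0.3 gives 1.26 and ρ = 0.6 gives 1.84. Simulation gave 0.69, 1.26 and 1.84.
- The factor passes 1 at ρ = (1 − 0.683)/1.936 = 0.16.

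The direction is therefore not fixed. A correction for classification error alone does not cure the second case. In this symmetric two-class setting it divides by 2a − 1, so at ρ = 0.3 it would turn 1.26 into 1.263/0.683 = 1.85.

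**The case against.** The strongest reply is that much of this comes from silence. The article gives no assignment rule, and class assignment, entropy and correction methods are details commonly left to an analysis plan that is not shown. That stands. A reader might infer that each patient will be placed in the most likely pattern and analysed as if it were certain, but the text does not say so. Multinomial regression does not imply it either, because a bias-adjusted three-step analysis is itself a multinomial regression of class on covariates.

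Two further replies also stand. The article does not say that the ANOVA is run on session scores; its stated object is patients' characteristics. And a reader might conclude that anyone with a missing session leaves the analysis, whereas the mixed models named alongside keep such patients. The missing-form rates are assumptions, and automated warnings and reminders are planned. The 35% dropout mentioned in the background comes from cited literature, not from this trial's planning, and is not used here.

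What these replies do not remove is the named method. Repeated-measures ANOVA is written into the plan. If it is meant for repeated scores, it suits incomplete series of unequal length badly. If it is meant for baseline characteristics, these are not repeated measures and the method does not match its object. The wording needs changing on either reading.

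**Conclusion.** The point holds in a limited form and is minor. Naming repeated-measures ANOVA beside mixed models is redundant, and it brings requirements that these data may not meet. The possible loss, if it is run on ten session scores, is 10% to 65% of patients for 1% to 10% of forms missing independently, and about 40% at 5%.

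If patterns are treated as known, associations may be understated or overstated and the standard errors are incomplete. A general claim of bias towards zero is not supported: it holds for variables unrelated to the trajectory within class, but it can reverse when patterns predict treatment outcome. These sizes rest on assumed class numbers, separation, accuracy and correlation, none of which the article gives.

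A reader might also infer that the objective on therapeutic alliance depends on this sequence. It does not. The secondary outcomes section separately plans to analyse the association of alliance with outcome and modality, and the additional analyses also relate change in distress to alliance scores. The pattern work is exploratory and conditional on several patterns being found. The primary analysis uses linear mixed models without the patterns and is unaffected.

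**What to change.** In the section on additional analyses {20b}:

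1. Delete the repeated-measures analyses of variance and use only the mixed models already named for repeated scores.
2. Add a sentence stating that, where patterns are related to patient characteristics or outcome, classification error will be carried forward by a bias-adjusted three-step method (maximum-likelihood or BCH correction), with entropy reported.
3. Where outcome is the dependent variable, state that independence of outcome and session scores within class will be checked, because the correction relies on it.

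The cost is wording and slightly more programming; no new data are needed. The downside is wider confidence intervals, which reflect the uncertainty that is really there.

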### Methods in analysis to handle protocol non-adherence and any statistical methods to handle missing data {20c}

The analysis will follow an intention-to-treat strategy. As missing values will be lessened by Qualtrics quality control strategies, no imputation plan is considered in advance.

### Plans to give access to the full protocol, participant-level data, and statistical code {31c}

Non-identifiable datasets can be made available by the principal investigators upon reasonable request and in agreement with the research collaboration and data transfer guidelines of the University of Barcelona. The current document outlines the full protocol.

### Oversight and monitoring

#### Composition of the coordinating center and trial steering committee {5d}

This is a multi-center study coordinated by the University of Barcelona in collaboration with the Open University of Catalonia. The main trial team is formed by two principal investigators (AM, GF) overseeing all aspects of the study, training of staff, and taking supervision of the clinical development of the interventions. They will meet weekly to monitor the progress with specific subgroups of the research team and with the trial coordinator. The latter, in coordination with the other members of the research team, will manage participant recruitment and treatment allocations, organize data entry, and monitor safeguarding data quality.

#### Composition of the data monitoring committee, its role, and reporting structure {21a}

An independent data monitoring committee was not deemed necessary given that this is a trial focused on behavior, and adverse events, if any, are expected to be minimal.

#### Adverse event reporting and harms {22}

As indicated previously, adverse events, if any, are expected to be minor due to the nature of the interventions. Regarding the intervention with VR, measures will be taken to prevent the occurrence of side effects arising from the use of VR devices that can be annoying or temporarily affect normal activity. Under certain conditions, the use of these devices can produce mild discomfort related to dizziness, nausea, headache, or eye dryness in some users. These discomforts can arise at any time throughout and beyond the therapy sessions. Currently, the factors that increase the risk of these unwanted reactions are known [53], and we will take measures to prevent them:
The virtual environments will be designed to be stable so that any movements will arise only from the user’s action.These movements will be reduced to a minimum by using techniques such as teleportation, which reduces the side effects of the simulation to almost zero.The participants will be instructed to immediately report any side effects to the therapist, who will interrupt the session until the complete disappearance of any nuisance.At the end of each session, participants should remain seated for a few minutes until it is clear that side effects are not present. If there is any discomfort, even to a small degree, they will remain seated, accompanied by the therapist until their complete recovery.

Apart from this VR-related dizziness, no harmful effects have been identified in the psychological treatments included in the study. However, at the end of each session, the presence and type of adverse events reported by the participants or observed by the investigators will be systematically recorded. The frequency, severity of all the detected harms, and causal relation to the treatment interventions will be analyzed and reported in forthcoming publications.

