The PCT therapy protocol will be based on the case conceptualization as described by Winter and Procter [34] and on a series of texts describing the applied form of PCT [16, 25, 33] as well as on previous literature on PCT for adult depressive patients [35]. These include detailed objectives and tasks for each session that are summarized here.

In the first session, patients are welcomed, their complaints are clarified, and their constructions about themselves and the problems they face are explored (including attributions and possible solutions). In the second session, the RGT is administered, and in the third session, some of the results of the grid analysis are discussed with the patient in an effort to reach an enriched view of themselves and their problem(s). Any diagram used for this exploration of identity will be two-dimensional (2D). Sessions 4 to 9 will be focused on the different aspects of the construct system which need further exploration and reconstruction (cognitive conflicts, construction of “ideal self,” construct differentiation, constriction, family constructs, etc.). As needed, according to the details of each particular case, changes occurring in therapy will be related to the construction of self and others reflected in the results of the RGT. At the end of the ninth session, patients will be asked to rate again the grid elements with the same personal constructs elicited in session 2. In the tenth session, results of this end-of-therapy grid will be visualized and discussed, along with future prospects and elaboration of their personal projects.

The PCT-VR therapy protocol will be identical to the one just described with the exception of the sessions (mainly 3 and 10) in which the constructions of self and others derived from the grid analysis are visualized and explored with the VR application EYME, instead of 2D displays. The head-mounted display used is either Oculus Go or Oculus Quest.

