#### Client change interview [51]

This semi-structured interview was created to assess the changes produced throughout therapy, the useful and adverse effects of interventions from the patient’s perspective. Patients are asked about the positive and negative changes they have experienced with the intervention. Questions are also asked about the attribution of such changes, and their probability of occurrence without intervention. It is administered after completion (post-treatment), and its function is to identify both changes that patients are aware of (in their own words) and adverse effects (too often neglected in psychotherapy research). All these aspects might go unnoticed with standardized questionnaires.

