#### Participant timeline {13}

Table 1 and Fig. 1 show the scheduling of evaluations and the participant timeline, respectively.

**Table 1 Tab1:** Schedule of assessments

	Pre-randomization	Post-randomization		
	Screening/baseline	Intervention (every session)	Post-treatment	6-month follow-up
SCV	X			
MINI	X		X	
BDI-II	X		X	X
DASS-21	X		X	X
CORE-OM	X		X	X
CORE-SFB		X		
SRS		X		
CRES-4				X
LSS	X			X
CCI			X	

*Abbreviations*: *SCV*, sociodemographic and clinical variables; *MINI*, International Neuropsychiatric Interview, *BDI-II*, Beck Depression Inventory second edition; *DASS-21*, Depression, Anxiety, and Stress Scale; *CORE-OM*, Clinical Outcomes in Routine Evaluation-Outcome Measure; *CORE-SFB*, Clinical Outcomes in Routine Evaluation-Short Form Version; *SRS*, Session Rating Scale; *CRES-4*, Consumer Reports Effectiveness Scale; *LSS*, Life Satisfaction Scale; *CCI*, Client Change Interview

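### Apart from the boosters and a suicide-risk alert, no general adverse-event collection is scheduled in follow-up or for patients who stop attending, and the post-treatment interview is not named as a harms source

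*Protocol article*

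**What the plan says.** The section Adverse event reporting and harms {22} lists dizziness, nausea, headache and eye dryness as possible mild effects of the VR devices and states: "These discomforts can arise at any time throughout and beyond the therapy sessions". It gives one systematic recording point: "at the end of each session, the presence and type of adverse events reported by the participants or observed by the investigators" are to be recorded. It adds an instruction for the VR sessions: "The participants will be instructed to immediately report any side effects to the therapist", who then interrupts the session. It ends with a commitment to analyse and publish how often harms occur, how severe they are and whether treatment caused them.

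Other sections add further contacts. Intervention description {11a} sets at most 10 sessions, "with one or two booster sessions at about 3 months after the tenth session", and uses VR mainly in sessions 3 and 10. The Client change interview section names adverse effects among the things the interview is meant to find: "It is administered after completion (post-treatment), and its function is to identify both changes that patients are aware of". Table 1 places it at post-treatment only. Plans for assessment and collection of outcomes {18a} describes the 6-month assessment as an emailed link to questionnaires. It also provides an automatic warning to the team when answers show a patient at risk, with suicidal ideation as the example. Under Plans to promote participant retention {18b}, patients who withdraw are asked why and encouraged to complete the follow-up questionnaires.

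**The concern.** The plan acknowledges that harms can occur outside sessions but attaches its systematic record to sessions. Once sessions end, or a patient stops coming, that record ends too. The trial continues to observe patients until the "6-month follow-up", but for efficacy and satisfaction rather than for harms.

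What is at stake is the harms report. Events not asked about during follow-up cannot be recovered reliably afterwards. A short list of late harms could then reflect when patients were asked rather than how they fared. This matters somewhat more here because the protocol dispenses with a data monitoring committee on the expectation that adverse events will be minimal, and plans no audits. The adverse-event record is what would test that expectation.

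**Working it through.** The protocol states no figure to reproduce, and the point depends on no sample size, error rate or event rate. The check sets the collection points side by side.

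| Period or patient group | General adverse-event collection stated | Other partial route |
|---|---|---|
| Sessions 1 to 10 | End of every session ({22}) | Immediate report to the therapist ({22}) |
| Post-treatment | Client Change Interview, once (interview section, Table 1) | Questionnaires with risk warning ({18a}) |
| About 3 months after session 10 | End of each of the one or two boosters ({11a} with {22}) | None stated |
| After the last booster, up to and including the 6-month assessment | None | CORE-OM and BDI-II scores, risk warning (Table 1, {18a}) |
| After a patient stops attending | None stated | Reason for withdrawal asked; follow-up questionnaires encouraged ({18b}) |

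1. Treatment phase. An effect that starts after session 3 can still be reported at session 4. The text does not say whether the end-of-session record asks about the interval since the previous session, but nothing excludes it.

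2. Session 10. This is a main VR session with no regular session after it. The post-treatment interview follows it, has adverse effects as a stated purpose, and is done by a researcher who has not met the patient before ({18a}). This exposure is therefore covered.

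3. Follow-up. Table 1 lists five instruments at 6 months: BDI-II, DASS-21, CORE-OM, CRES-4 and LSS. They measure symptoms, distress, satisfaction with treatment and satisfaction with life. None is described as asking about events. The interview is not repeated.

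4. Risk warning. It responds to questionnaire answers and alerts the team. It is not described as an adverse-event record, and a hospital admission or a crisis that had resolved before the questionnaire need not trigger it.

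5. Early leavers. The session-end record stops with attendance. The interview is described as following completion, and the text does not say whether it is offered to those who leave. The question about reasons for withdrawal could reveal a harm, but nothing links the answer to the harms record.

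6. Link to the analysis. The harms section commits to analysing detected harms but mentions only the session-end record. Whether adverse effects found in the interview enter that analysis is unstated.

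The gap therefore lies in the last two rows of the table, together with the missing link in step 6.

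**The case against.** The strongest case on the other side is that the plan has more harms contacts than its harms section suggests. The post-treatment interview and the boosters are real collection points. CORE-OM covers risk and is given at 6 months, BDI-II shows symptomatic worsening, and the risk warning applies at every stage including follow-up. The protocol describes the VR effects as mild and temporary, and nothing suggests they first appear weeks later. Session-end recording applies in all arms, so no bias between arms is shown. Table 1 carries no adverse-event row in any column, not even for the sessions where recording is plainly promised, so its silence alone proves little. The exact wording of the recording question is a detail an article may leave to the case report form.

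Most of this stands, and it rules out two stronger readings. A reader might infer that adverse events are recorded only at session end and that delayed effects of the session-10 VR exposure are largely missed. The documents do not support this, because the interview comes after that session and asks about adverse effects. A reader might also try to size the gap by the share of calendar weeks without a session, or by the 6-year re-admission percentages in the Background. Neither works. Calendar time is not a share of harms, and the start of the 6-month period is not fixed. The re-admission figures come from hospital-treated patients, most of whom returned with recurrent depression rather than a treatment harm.

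What the objection does not answer is the 6-month assessment and the early leavers. Symptom scores and a risk warning do not record an event, its severity or its relation to treatment. Nor is this mere condensation: the article states its recording point, prints its assessment schedule, and says under {31c} that it outlines the full protocol.

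**Conclusion.** The point holds in a limited form and is minor. Followed as written, the plan collects no general adverse-event information after the boosters, at the 6-month assessment, or from patients who stop attending, and it does not say how the post-treatment interview feeds the harms analysis. Late events such as a hospital admission would be under-recorded.

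The number of events missed cannot be derived from the documents, and no figure is offered. The effect is an absolute under-count of late harms; a difference between arms is not shown, and the primary outcome and its inference are untouched.

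The conclusion rests on two readings: that post-treatment means shortly after session 10, before the boosters, and that the 6-month questionnaires contain nothing beyond what Table 1 lists. The text does not say whether the 6 months run from session 10 or from the last booster, or whether boosters use VR. Neither affects the conclusion about the 6-month assessment.

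**What to change.** In Adverse event reporting and harms {22} and in Table 1:

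- Add a short look-back adverse-event question, covering the time since the last session or assessment and naming hospital admission and self-harm. Use it in all three arms, in the post-treatment and 6-month questionnaire links already sent.
- Send these links, with the question, to patients who left treatment early as well.
- Optionally, add the same question to the pre-session CORE-SFB link, which settles whether the interval between sessions is covered.
- State that adverse effects reported in the Client Change Interview enter the harms analysis. Keep the end-of-session record.

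The cost is a few items in existing electronic forms and an amendment. Patient burden rises slightly, and the count of minor events will be higher, so the report should show severity alongside frequency. No extra visit or staff is needed.
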